### Dysphagia outcome and severity scale (DOSS)

11.3

The DOSS is a simple, easy-to-use, 7-point scale developed to systematically rate the functional severity of dysphagia based on objective assessment and make recommendations for diet level, independence level, and type of nutrition.^[40]^ The score ranges from 1 (severe dysphagia) to 7 (normal in all situations). DOSS scores will be recorded in the eCRF at the screening, day 2, 7 ± 1 days and 14 ± 1 days visits.

### Murray secretion severity rating scale (SSS)

11.4

The SSS is a simple, easy-to-use, 4-point scale developed to systematically rate the graduation of accumulated secretions within the pharyngolarynx and trachea during an objective assessment using FEES^[41]^ by trained clinicians. The score ranges from 0 (normal) to 3 (severe). Secretion severity will be assessed by the IFRC using the SSS observed during FEES at screening and on day 2 (approx. 24–60 hours) after completion of the final PES treatment. SSS scores will be recorded in the eCRF.

### Yale pharyngeal residue severity rating scale (YRS)

11.5

The Yale Pharyngeal Residue Severity Rating Scale (YRS) is a reliable, validated, anatomically defined, and image-based five-point ordinal rating scale to determine severity of post-swallow pharyngeal residue location (vallecula and pyriform sinus) and amount (none, trace, mild, moderate, and severe) during FEES.^[42]^ Residue severity will be assessed by the IFRC using the YRS observed during FEES at screening and on day 2 (approx. 24–60 hours) after completion of the final PES treatment. YRS scores will be recorded in the eCRF.

### Global dysphagia severity rating scale (GDS)

11.6

The Global Dysphagia Severity ratings scale (GDS) is a simple, easy-to-use, 4-point scale developed to systematically rate the severity of dysphagia during an objective assessment using FEES^[43]^ by trained clinicians. Dysphagia severity will be assessed by the IFRC using the GDS observed during FEES at screening and on day 2 (approx. 24–60 hours) after completion of the final PES treatment. GDS scores will be recorded in the eCRF.

## Data collection, management, and confidentiality

12

Study data will be collected and stored in a validated, password protected electronic data capture (EDC) system using eCRFs. Designated site personnel will be trained to enter data into the web-based, study-specific EDC system. The EDC system allows for tracking of all data elements and any changes made (full audit trail).

As per ISO14155: 2011 (section 6.3, 6.7), in order to assure appropriate conduct of the study, participating investigators and/or institutions shall provide direct access to source data during and after the clinical investigation for monitoring, audits, EC review and regulatory inspections. Patient confidentiality will be strictly held in trust by the investigators, study staff, the sponsor(s) and their agents to the extent allowed by law, including Personally Identifiable Information. Investigators will ensure protection of patient personal data and that all reports, publications, and any other disclosures, except where required by law are identified only by the patient identification number and site identification number to maintain patient confidentiality. All patient study records will be kept safely in an access-controlled area. At the end of the study, all records will continue to be kept in a secure location for at least 15 years (or per local regulations) after the study is closed.

## Clinical monitoring, quality assurance and quality control

13

Clinical site monitoring will be conducted to help ensure that the rights and well-being of patients are protected, that the reported study data are accurate, complete, verifiable and that the conduct of the study is compliant with the currently approved protocol/amendment(s) and with applicable regulatory requirement(s) including ISO14155: 2011 and ICH GCPs. The sponsor or designee Clinical Research Organization (Syntactx EU Limited) will train all Investigators and relevant study staff at or prior to site initiation and monitor the study throughout its duration. Study monitors will visit each site at appropriate intervals to review clinical data for accuracy and completeness and to help ensure compliance with the protocol. A study termination (close-out) monitoring visit will be conducted at the completion of the study. A Monitoring Plan is established to outline roles and responsibilities.

## Study governance

14

Phagenesis Ltd is the study Sponsor and has the overall responsibility for the conduct and safety of the study. The sponsor is responsible for assuring that the study meets the regulatory requirements of applicable competent authorities and governing institutional review boards/ethics committees. A Trial Steering Committee is established and is responsible for general oversight of the study. This committee will meet periodically to monitor clinical site progress and protocol compliance. The committee will be responsible for reviewing the final results. Clinical trial liability insurance is provided by the Sponsor for all study participants in accordance with applicable laws and regulations of the countries where the trial will be conducted to provide financial compensation in case of harm by study measures, if that should occur.

## Safety oversight

15

A Medical Monitor (MM), in conjunction with the sponsor, will review adverse events (AE) of interest listings and will flag any events that require further review/investigation or if a safety review meeting is required. The MM is independent of Phagenesis and any study site. The MM's roles and responsibilities are outlined in a Safety Management Plan. An independent Data Monitoring Committee (DMC) will be established for the purposes of this study. The DMC will be responsible for monitoring aggregate safety information and the impact of AEs of interest on the safety and well-being of the patients, particularly if events relate to the Phagenyx system and study procedures. Safety and efficacy will be checked at the interim analysis. The DMC may recommend that the sponsor modify or stop the study based on safety information, or for efficacy/ futility. At the planned Interim Analysis, the DMC will also make recommendations on all pre-specified decision rules for study termination, continuation or adaption (e.g., Sample Size Re-estimation and/or population enrichment). The DMC members will be independent of Phagenesis Ltd and any participating study site. The DMC's roles and responsibilities will be outlined in a DMC Charter.

## Protocol amendment(s)

16

Any revision/amendment(s) to the Protocol or Informed Consent documents will be submitted to applicable local/national ethics committees/institutional review boards in accordance with applicable regulations. Approvals will be obtained prior to implementing Protocol revisions at the sites.

## Statistical considerations

17

### Statistical hypotheses

17.1

The primary effectiveness analysis (Finkelstein-Schoenfeld (FS)^[32]^ (win-ratio) statistic) is on the composite of two endpoints in the following hierarchy based on clinical priorities:

1.Swallowing safety based on worst PAS score in series of up to 4 boli using thin stimuli (water) for each patient as determined by a FEES assessment on day 2 (approx. 24–60 hours) after completion of the final PES treatment, converted to a trichotomized ordinal response of safe (PAS 1–3), penetration (PAS 4–5), or aspiration (PAS 6–8).2.DOSS score determined by bedside assessment 7 ± 1 days after completion of the final PES treatment.

Using the FS approach, each treatment arm patient will be compared to each control arm patient and a winner/loser determined. Comparisons are made hierarchically as defined above so that if the treatment arm patient performs better than the control arm patient with respect to the first hierarchy level (PAS) outcome then the treatment arm patient gets a score of +1 (winner) otherwise a score of −1 (loser) is assigned. If the first hierarchy level comparison is tied then the comparison is done with respect to the second outcome (DOSS) and the same scoring procedure is followed. The FS-statistic is based on the mean of the scores obtained from all such comparisons. If P is the probability that a randomly picked treatment arm patient performs better than a randomly picked control arm patient, then the expected value of the FS-statistic is given by 2 (P – 0.5). The hypothesis of interest is a one-sided null: H_0_: *P* ≤ .5 vs the one-sided alternative H_1_: *P* > .5. PAS and DOSS scores are ordinal outcomes. For each pair of patients evaluated (a pair being composed of one treated patient and one control patient), a binary outcome is derived that indicates whether the treated patient or the control patient performs better.

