### Fiberoptic endoscopic evaluation of swallowing (FEES)

10.2

FEES is recognized, validated, and routinely used in many hospitals across Europe for instrumental dysphagia assessment. It is considered a gold standard technique for airway- and swallow-safety^[19–22]^ assessment and is the recommended methodology in current guidelines.^[20,36]^ Complications such as discomfort, gagging, vomiting, vaso-vagal syncope, anterior or posterior epistaxis or rare complications such as laryngospasm are expected to occur in < 1% of examinations.^[23]^ In this study, FEES will be performed via nasal induction of an endoscope into the pharynx with visualization of the larynx (details are given elsewhere ^[1]^). FEES assessments will be conducted at screening and on day 2 (approx. 24–60 hours) after completion of the final PES treatment. The FEES assessment will capture:

1 × 30 second video prior to any boli stimuli to assess secretions severity.4 × 10 ml swallow trials with thin liquid (water, International Dysphagia Diet Standardisation Initiative (IDDSI ^[37]^) level 0) stimuli.2 × 10 ml swallow trials with semi-solid (puree, IDDSI level 4) stimuli.2 × non-obligatory soft and bite-sized swallow trials with solid (white bread without the crust approximately 1.5 cm × 1.5 cm × 0.5 cm, IDDSI level 6) stimuli presented only to patients in whom no residues are observed on thin liquid and puree swallow trials.

Data will be entered in the eCRF. Coded video records will also be provided to the IFRC for further analysis and validation of local PAS scores for the thin liquid stimuli (for (re)training purposes only). IFRC members will score videos blinded to the site and other member's scores to allow unbiased scoring. FEES results will not be scored in duplicate, PAS ratings by the local site investigator will be used for all primary endpoint analyses and clinical decision-making.

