### FEES stopping criteria

10.3

If gross aspiration (PAS ≥6, see below) of two consecutive bolus trials of the same consistency are observed, that consistency should be stopped and the investigator administering the FEES (or trained and authorized designee) should decide either to move to the next consistency (to assess any potential dietary modification) or terminate the FEES. A ‘Stop’ may be applied at any time if the investigator administering the FEES (or trained and authorized designee) feels it to be unsafe for the patient to continue.

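### A thin-liquid series ended early as unsafe, before any aspiration is seen, is scored as observed and can outrank a completed series with one aspiration

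*Protocol article*

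**What the plan says.** Sections 6.1 and 17.1 of the Protocol article define the first level of the primary hierarchy as "Swallowing safety based on worst PAS score in series of up to 4 boli using thin stimuli (water) for each patient", taken from the day-2 FEES and "converted to a trichotomized ordinal response of safe (PAS 1–3), penetration (PAS 4–5), or aspiration (PAS 6–8"). Section 10.2 plans "4 × 10 ml swallow trials with thin liquid (water", IDDSI level 0).

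Section 10.3 gives two ways for the series to end early:

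- **Score-based stop:** "If gross aspiration (PAS ≥6, see below) of two consecutive bolus trials of the same consistency are observed, that consistency should be stopped".
- **Discretionary stop:** "A ‘Stop’ may be applied at any time if the investigator administering the FEES" or a trained designee "feels it to be unsafe for the patient to continue". No PAS value is attached.

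The article sets no minimum number of boli and gives no category to a series ended by the discretionary stop. Section 10.2 adds that "PAS ratings by the local site investigator will be used for all primary endpoint analyses and clinical decision-making". Under 3.1 and 10.2, the independent FEES committee's review of the local PAS scores serves (re)training only. DOSS decides a pair only when the PAS categories tie (17.1).

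**The concern.** A worst score over several boli can only stay the same or get worse as boli are added. If the number of boli is fixed, that is harmless. Here it can be cut short, and one permitted reason is that the assessor thinks continuing is unsafe. A patient about whom the assessor was worried may thus have fewer chances to show aspiration and be ranked better for it.

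The primary objective (2.1) is to reduce the severity of unsafe swallows, so a ranking that can run the wrong way at the first level matters. The second level cannot repair it, because DOSS is not reached once the PAS categories differ. Every randomized patient had a PAS of 6 or more at screening (3.1, section 5), so a safety stop on day 2 is a realistic event.

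**Working it through.** **1. The two stops under the scoring rule.** After two consecutive scores of 6 or more, the worst score is already 6–8, so further boli cannot change the category. After a discretionary stop prompted by one visible aspiration, the same is true. The problem is confined to discretionary safety stops made before any score of 6 or more.

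**2. A pair compared under the written rules.**

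| Patient | Thin boli and PAS | Worst PAS | Category |
|---|---|---|---|
| X | 3, then stopped as unsafe | 3 | safe |
| X′ | 5, then stopped as unsafe | 5 | penetration |
| Y | 2, 2, 2, 6 (completed) | 6 | aspiration |

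X beats Y at level 1, and so does X′. DOSS is not consulted in either comparison.

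**3. How much a shortened series can hide (illustrative).** Section 17.2 assumes that 50% of controls and 65% of PES patients reach PAS 1–5, so 50% and 35% remain at 6–8. The article does not say that these rates refer to four completed boli; I assume it here. With independent boli (also an assumption), the per-bolus probability is p = 1 − (1 − a)^(1/4):

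- control: 1 − 0.50^(1/4) = 0.159
- PES: 1 − 0.65^(1/4) = 0.102

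The chance of being classed aspiration after k boli is 1 − (1 − p)^k. Boli within one patient and session are unlikely to be independent, so beta-binomial versions with assumed within-patient correlations follow.

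| Correlation | Control, k = 1 / 2 / 3 / 4 | PES, k = 1 / 2 / 3 / 4 |
|---|---|---|
| 0 | 15.9 / 29.3 / 40.5 / 50% | 10.2 / 19.4 / 27.6 / 35% |
| 0.2 | 20.9 / 34.1 / 43.2 / 50% | 13.4 / 22.7 / 29.6 / 35% |
| 0.5 | 29.6 / 40.1 / 46.0 / 50% | 19.3 / 27.0 / 31.7 / 35% |
| 0.8 | 41.1 / 45.9 / 48.4 / 50% | 27.5 / 31.5 / 33.6 / 35% |

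The direction is the same in every row. The amount hidden shrinks as boli become more alike.

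**4. Effect on the contrast between arms (frequencies assumed).**

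- Stops unrelated to score or arm: 10% of each arm stopped after one bolus, independent boli. Observed non-aspiration is 1 − (0.9 × 0.50 + 0.1 × 0.159) = 53.4% in controls and 1 − (0.9 × 0.35 + 0.1 × 0.102) = 67.5% on PES. The difference is 14.1 points instead of 15.
- Stops that follow true swallowing safety: if 4% of controls and 2% of PES patients are true aspirators stopped before aspiration is seen, the difference is (50 − 4) − (35 − 2) = 13 points. With 10% and 5% it is (50 − 10) − (35 − 5) = 10 points.

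**5. The plan's own sample size.** Section 17.2 states at least 90% power with 100 per arm. For PAS alone (50% against 65%, one-sided 0.025) power at 100 per arm is 57%. A simulated Finkelstein-Schoenfeld test on PAS and DOSS gave 75% to 98%, depending on inputs the article does not state (DOSS standard deviation 1 to 2, and the split between safe and penetration); PAS and DOSS were taken as independent and the interim analysis was ignored. The stated power is neither confirmed nor refuted, and this point does not rest on it.

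**The case against.** - **The bolus limit has an innocent explanation.** The score-based stop needs it, since those patients may receive fewer than four boli and stay in the aspiration category. That explains the phrase, but the text does not confine it to that stop. Read as written, a series ended by the discretionary stop also has a worst score and a category.
- **This could be left to the analysis plan.** Section 17.4 promises one before the interim analysis, and it is not shown. That plan may contain a rule. But a patient with one scored bolus is not missing under the published definition, so a missing-data rule would not obviously apply. The patient given no bolus at all is different: that is missing data, which the unseen plan may cover, and it is not part of this point.
- **The size is not documented.** This stands. The frequencies in step 4 are invented for illustration. The 10% control scenario means that one in five control aspirators (10 of 50) is stopped before any aspiration is seen. The only nearby figure, FEES complications in under 1% of examinations (10.2), concerns procedural events such as gagging or epistaxis and does not measure these stops.
- **The bias is conservative.** Assessors are blinded (3.1), and where stops follow swallowing safety the pull is towards no effect if PES works. No false-positive risk is shown.
- **Part of the record exists.** Section 11.1 already has PAS entered for each thin bolus, so the number scored can be recovered. The reason for stopping is not mentioned.
- **The remedy is itself a judgement.** It counts as aspiration a patient in whom none was seen, on the strength of a recorded stop reason. That is a fair cost, and the sensitivity analysis is there to test it.

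**Conclusion.** The point holds in limited form. The endpoint definition and the discretionary stop together allow a patient whose test was ended as unsafe, with no PAS of 6 or more yet seen, to be ranked above a patient who completed four boli and aspirated once. This follows from the text and needs no assumption. Nothing else in the article corrects the score.

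The size is unknown and may be small. If PES improves swallowing and stops follow true safety, more sham patients would be scored too favourably and the PAS contrast would shrink. If stops are unrelated to swallowing, the effect is mainly blurring.

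A reader might infer that the planned 15-point difference will fall to 10. The article does not support that: it gives no stop frequency, and 17.2 does not tie its rates to four completed boli, so they may already describe the endpoint as measured. Nor does it follow that the rule generally rewards unsafe swallowing, since every observed aspiration is still placed in the worst category. No effect on the power of the PAS/DOSS composite has been shown.

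**What to change.** In 6.1 and 17.1, state that a day-2 thin-liquid series that was started but ended early for swallowing safety, with no PAS of 6 or more observed, is ranked in the aspiration category for level 1. Record the reason for any early stop in the eCRF, so that stops unrelated to swallowing, such as a technical failure, are not reclassified. Report the worst PAS as observed as a sensitivity analysis. Settle the rule before the interim analysis, at which efficacy is examined (section 15). The clinical stopping rule in 10.3 need not change.

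The cost is one sentence in the endpoint definition, one eCRF field and one extra analysis, with no added procedure. The drawback is that a few patients stopped out of caution will count as aspirators, and their category then depends on the blinded assessor's recorded reason.

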**Figure 1 F1:**
[figure not shown]
Study flowchart.

An Independent FEES Review Committee (IFRC), external to the study sites, will be established for analysis of all study-related FEES assessment parameters and to confirm/validate the PAS scoring of the local clinical FEES assessor(s). FEES results will not be scored in duplicate but discrepancies in ratings between the local team and IFRC, or concerns about the quality of submitted records will be reviewed and discussed with the local team for (re-)training purposes only. All FEES records will be coded so that records are only identified by site number, bolus number, patient number, and study visit (i.e., screening or follow-up). The IFRC will be blinded to the treatment assignment as well as the actual treatment received.

Six or more investigational academic hospital sites across Europe are anticipated to participate in this study. Factors considered for site qualification of ICUs include, but are not limited to: potential number of suitable patients, availability, and experience of conducting FEES. The enrolment period is expected to be approximately 48 months from the time of first patient recruitment to the final study visit. Each patient's participation will last for up to 90 days with assessments at the following intervals: screening, baseline, day 2 (approx. 24–60 hours), 7 ± 1 days, 14 ± 1 days or hospital discharge (whichever is first) after completion of the final PES treatment. 30-day and 90-day mortality data will also be collected from the patients (electronic health record) medical notes - this will not require an additional visit but a phone call may be conducted depending on the patient's status. Dysphagic patients enrolled into the study will continue to receive nutrition as deemed appropriate by the ICU team. Patients with a nasogastric feeding tube in place at the time of screening/enrolment will have their nasogastric tube replaced with the Phagenyx Catheter since the Phagenyx Catheter may also be used to deliver nutrition to the patient as required for up to 30 days after placement.

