## Randomization

8

Patients will be randomly allocated to PES treatment or sham (comparator) according to a permutated block randomization stratified by site and reason for ICU admission (neurological vs non-neurological according to APACHE IV diagnostic criteria) using a random mixture of blocks of size 2 and 4. The randomization ratio will be 1:1. The PES treater(s) at site shall not be blinded to the patient's randomization assignment in order to be able to deliver PES treatment or sham (comparator). Randomization assignment will be via the web-based study EDC with access restricted to authorized PES treaters. The randomization page of the EDC will only become available once the patient is confirmed to have met all of the inclusion/exclusion criteria and the treatment catheter is successfully placed and tolerated.

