### Sample size determination

17.2

Sample size calculations were carried out using simulations and are adjusted for interim analysis. Assuming that 50% of control patients will move from PAS score of 6–8 at baseline to a PAS score of 1–5 post-intervention and the corresponding number of patients in the PES treatment group is 65% (15% effect-size) and that the PES treatment group will benefit with a mean increase of 0.7 points on the DOSS score, 100 patients per arm will be required to achieve a power of at least 90%. Thus N_planned_ = 200 is the minimum sample size (unless the study is stopped early for futility at the only interim analysis). To allow for adaptations in design with respect to sample size and population enrichment, a maximum (evaluable) sample of N_max_ = 360 is pre-specified. To account for a 10% lost-to-follow-up, a maximum of 400 patients will be recruited.

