### Statistical analyses

17.4

Tabulations will be produced for appropriate demographic, baseline, effectiveness and safety parameters. For categorical variables, summary tabulations of the number and percentage within each category (with a category for missing data) of the parameter will be presented. For continuous variables, the mean, median, standard deviation, minimum and maximum values will be presented. Time to event data will be summarized using Kaplan–Meier methodology using 25th, 50th (median), and 75th percentiles with associated 2-sided 95% confidence intervals, as well as percent of censored observations. Formal statistical hypothesis testing will be conducted at the 1-sided, 0.025 level of significance. A Statistical Analysis Plan (SAP) will detail all statistical analyses planned for this study and will be established prior to the planned Interim Analysis.

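### The primary Finkelstein-Schoenfeld test pairs patients across the randomisation strata: it stays valid, but is conservative and gives up some power if admission reason is prognostic

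*Protocol article*

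**What the plan says.** Section 8 of the Protocol article allocates patients by "permutated block randomization stratified by site and reason for ICU admission", in blocks of 2 and 4; section 3.1 names the same two factors. "The randomization ratio will be 1:1". Section 3.1 also says: "Six or more investigational academic hospital sites across Europe are anticipated to participate in this study". Six sites and two admission groups make at least 6 × 2 = 12 randomisation strata.

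Section 17.1 then sets out the primary test without reference to these strata:
- Pairing: "each treatment arm patient will be compared to each control arm patient and a winner/loser determined".
- Statistic: "The FS-statistic is based on the mean of the scores obtained from all such comparisons".
- Hypothesis: "If P is the probability that a randomly picked treatment arm patient performs better than a randomly picked control arm patient", then the one-sided null is that P is at most 0.5.

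Section 17.4 adds: "Formal statistical hypothesis testing will be conducted at the 1-sided, 0.025 level of significance". Section 17.2 gives at least 90% power with 100 patients per arm and mentions no stratum effect.

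**The concern.** Blocked randomisation within strata balances the arms on the stratification factors. If those factors predict outcome, the pooled statistic varies less from one randomisation to another than an unstratified variance formula supposes. The standard error is then too large, the test rejects less often than 2.5% under the null, and power is lost under the alternative.

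The pairs show the same thing. A neurological PES patient compared with a non-neurological control contributes a win or loss that partly reflects the difference between the groups. If 40% of patients were neurological (an assumption), each arm of 100 would have 40 and 60, and within-group pairs would number 40² + 60² = 5,200 of the 100 × 100 = 10,000. The other 48% would cross admission groups.

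At stake is efficiency: power that could be had from data already collected at randomisation.

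**Working it through.** **1. The plan's own figure.** Section 17.2 assumes that "50% of control patients will move from PAS score of 6–8 at baseline to a PAS score of 1–5 post-intervention", against 65% with PES, and a DOSS gain of 0.7 points. It gives no DOSS standard deviation (SD), no PAS-DOSS correlation and no split of responders into safe and penetration. With SD 1.3 to 2.0, correlation 0 or 0.5 and a safe share of 0.5 to 1.0, the simulated all-pairs test has 75% to 96% power at 100 per arm (one-sided 0.025, no interim). The stated 90% is reachable but cannot be pinned down. Only differences between tests are therefore read below.

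**2. The two tests.** Let u_i be patient i's wins minus losses against all other patients, with full ties scored 0.
- All pairs: T = sum of u_i over PES patients; V = n1·n0/[N(N−1)] × Σu_i²; reject if T/√V > 1.96.
- Within stratum: compute T_s and V_s from pairs inside stratum s only; reject if Σw_sT_s / √(Σw_s²V_s) > 1.96. With w_s = 1/(n_s+1) and 1:1 allocation, each stratum's mean score is weighted roughly by its size.

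**3. Error of the all-pairs test, by formula.** If strata carry a share r of the variance of the scores, the true variance is about (1−r) times the one used. The true one-sided error is 1 − Φ(1.96/√(1−r)).

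| r | Formula | Simulated, 12 strata |
|---|---|---|
| 0 | 2.5% | 2.2% |
| 0.1 | 1.9% | 2.2% |
| 0.2 | 1.4% | 1.4% |
| 0.3 | 1.0% | 1.0% |

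In the simulation, r is the stratum share of the latent outcome variance; its error is about 0.2 to 0.25 points. The formula never exceeds 2.5%.

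**4. Two strata (admission reason only), N = 200, SD 1.4.** Two separate simulations; every stratum input is assumed. In A, 40% of patients are neurological. Its moderate case has control aspiration of 65% vs 40% and mean DOSS of 3 vs 4; its strong case has 75% vs 33% and 2.7 vs 4.3. Both agree with the plan's 50% control response: 0.4 × 65 + 0.6 × 40 = 50.0 and 0.4 × 75 + 0.6 × 33 = 49.8. B sets the safe share of responders at 0.7.

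| Admission effect | Run | Power, all pairs | Power, within | Difference | Error, all pairs | Error, within |
|---|---|---|---|---|---|---|
| None | B | 86.4% | 86.1% | −0.3 | 2.65% | 2.6% |
| Moderate | A | 91.9% | 94.0% | +2.1 | 1.8% | 2.2% |
| Moderate | B | 83.4% | 87.1% | +3.7 | 2.0% | 2.5% |
| Strong | A | 90.4% | 95.5% | +5.1 | 1.2% | 2.7% |
| Strong | B | 84.3% | 91.4% | +7.1 | 1.0% | 2.4% |

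Run A used 2,000 replicates for power and 4,000 for error, so its standard errors are about √(0.9 × 0.1/2,000) = 0.7 points and √(0.025 × 0.975/4,000) = 0.25 points. The 2.7% is thus compatible with 2.5%. Inverting the formula in step 3, errors of 1.8% to 2.0% correspond to r of about 0.09 to 0.13, and errors of 1.0% to 1.2% to r of about 0.25 to 0.29.

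A third set of assumptions (SD 1.5, correlation 0.3, two strata) gives 87.5% vs 86.9% with no stratum effect. At a stratum share of 0.2 it gives 92.1% vs 94.1%, with error 2.0% vs 2.5%.

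**5. Pairing within site and admission reason.** Power under the third set of assumptions:

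| Strata | Stratum share | All pairs | Within, unweighted | Within, weighted |
|---|---|---|---|---|
| 12 | 0 | 88.1% | 85.7% | 86.3% |
| 12 | 0.1 | 87.3% | 87.7% | 88.7% |
| 12 | 0.3 | 89.7% | 93.5% | 94.5% |
| 24 | 0 | 88.0% | 82.9% | 85.7% |
| 24 | 0.3 | 89.2% | 92.6% | 94.4% |

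With no stratum effect the loss is about 2 to 5 points. Break-even with 12 strata is near a share of 0.1.

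**The case against.** Four arguments on the other side carry weight.

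- **The test is valid.** A reader might infer from the mismatch that the error rate is unsafe. It is not: the error stays at or below 2.5% apart from simulation noise, so a positive result is not weakened. This stands in full.
- **No shortfall in power is shown.** A reader might infer that the 90% target is missed because of the pooling. In run A the all-pairs test still reaches 91.9% and 90.4%. Run B falls below 90% even with no stratum effect and even when stratified in the moderate case, so there the cause is the inputs that the article does not state. This stands: the gain is relative to whatever power the trial has.
- **No stratum effect is documented.** The article names the factors but does not say that prognosis differs between them, and the entry criteria narrow the population (all have PAS 6 or above; prior dysphagia is excluded). That admission reason decides many pairs cannot be shown. This limits the size. Even so, the two-stratum test costs almost nothing if the effect is absent. The concern that stratifying can lose power applies to 12 to 24 small cells.
- **The SAP will give the detail, and all-pairs scoring estimates the stated P directly.** Section 17.4 does defer detail to an SAP that is not shown and may stratify. But section 17.1 already fixes pairing, statistic and P without strata, so a stratified SAP would have to be reconciled with it. The change of target is real and must be stated.

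**Conclusion.** The mismatch holds: randomisation is stratified by site and admission reason, while the stated primary test ignores both. The consequence is a possible loss of efficiency, with no excess of false positives. With pairs formed within admission reason, the change in power is about 0 points with no stratum effect, 2 to 4 points with a moderate one and 5 to 7 with a strong one; the all-pairs error is then about 2.5%, 2% and 1%. These figures assume 100 per arm, SD 1.4, the stated treatment effects within each stratum, and stratum differences that the article does not supply. No interim analysis was modelled. Confidence is high in the mismatch and in the direction of the effect, and low in its size. The article does not support a claim that the trial is underpowered for this reason, or that its significance level is wrong in a harmful direction.

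**What to change.** In section 17.1, before the interim analysis:
- Make the primary test a Finkelstein-Schoenfeld test with pairs formed only within admission reason (neurological / non-neurological), combined with pre-set size-based weights, for example 1/(n_s+1) applied to each stratum's sum of scores.
- Redefine P as the correspondingly weighted average of the within-stratum probabilities.
- Keep the all-pairs analysis as a sensitivity analysis.
- Do not pair within site-by-admission cells in the primary test; handle site in a supportive analysis, with small sites pooled.

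Align the SAP with this text. The cost is a short change to the wording and the analysis code; the stratum is known at randomisation and no patients are added. Two downsides should be stated: the target probability becomes within-stratum rather than marginal, and power may fall by a fraction of a point (0.3 to 0.6 in the calculations above) if admission reason is not prognostic.
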